## Exclusion criteria

### Sub-clusters (villages)

Villages are excluded from the study if:

- Not fulfilling inclusion criteria
- Village-authorities are opposed to the campaigns

### Individuals

Individuals are excluded from the study if:

- Not fulfilling eligibility criteria

In addition individuals are excluded for the analysis of the primary outcomes if:

- Already known HIV-positive
- Prior HIV-test < 3 months (window-period)

## Selection of villages, households and individuals

**Selection of communities:**

Before being informed if they are allocated to door-to-door or to pitso, the health center staff provides a list of ten villages within their catchment area that fulfill the eligibility criteria (see above) and that have not benefited from any sensitization or screening campaign in the past two years. From this list five villages will be randomly^[[1]](#footnote-1)^ chosen to receive the campaign (either door-to-door or pitso).

**Selection of households/place:**

- Door-to-Door approach: Within the villages the households are approached systematically starting from the chief’s place (moreneng), going to the periphery. A household is defined as one or several houses grouped together that are inhabited by one family. In case, a household is empty, the next household towards the periphery is chosen.
- Pitso approach: The pitso will be held at the place allocated by the village authorities, usually at the chief’s place (moreneng).

**Selection of individuals:**

- Door-to-Door: All members of a household (irrespective of age) will be proposed the integrated package including HTC.
- Pitso approach: All persons attending the pitso will be invited to receive the integrated package

## Outcomes measured

### Sources of outcomes

Sources of the different outcomes measured are the study-questionnaire (see annex 2), and the following official registers at the health centers: HTC-register, pre-ART register, ART-register, tuberculosis-suspect register

| *Outcome variable* | *Hypothesis* | *Source/Measure* | *Statistical Method* |
| --- | --- | --- | --- |
| **Primary outcomes** |  |  |  |
| 1. Proportion and absolute number of clients accepting HTC | Higher in door-to-door | Source: study-questionnaire | logistic regression |
| 1. Proportion and absolute number newly tested HIV-positive | Higher in door-to-door | Source: HIV-test result from Determine® & Double Check® (according national guidelines) [binary/count] | logistic regression |
| 1. Proportion and absolute number newly enrolled on chronic HIV/AIDS care within one month after the campaign of those newly tested during campaign | Higher in door-to-door | Source: study-questionnaire and pre-ART and ART-Registers. Enrolled (Y/N) [binary/count] | logistic regression |

| **Secondary outcomes** |  |  |  |
| --- | --- | --- | --- |
| 1. Proportion of first-time testers | Higher in door-to-door | Study-questionnaire [binary] | logistic regression |
| 1. Age of clients attending HTC | Lower in door-to-door | Study-questionnaire [cont] | t-test/ranksum test |
| 1. Sex of clients attending HTC | Proportion of male testers is higher in door-to-door | Study-questionnaire [binary] | logistic regression |
| 1. Proportion newly tested HIV-positive with advanced disease (WHO-stage 3 or 4) | - | Study-questionnaire [binary] | logistic regression |
| 1. Average CD4-count of clients newly tested HIV-positive | - | On-site CD4-count using PIMA^TM^ [cont] | t-test/ranksum-test |
| 1. Absolute number and proportion of clients screened positive for tuberculosis | - | Study-questionnaire [count/binary] | logistic regression |
| 1. Absolute number and proportion of clients positively screened for tuberculosis who bring their sputum to the facility within ≤ 5 days | - | Study-questionnaire and tuberculosis-suspect register | logistic regression |
| 1. Absolute number and proportion of clients bringing their sputum bottles who have a positive direct sputum smear | - | Study-questionnaire and tuberculosis-suspect register | logistic regression |
|  |  |  |  |

Table 2 Primary and secondary outcomes measured in the study

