## STUDY SETTING

The study will take place within the catchment areas of Seboche and Paray Mission hospital. Both hospitals belong to the Christian Health Association of Lesotho (CHAL). Seboche hospital is situated in the northern Lesotho, district Butha Buthe, has an estimated population of about 55’000 and an estimated adult HIV-prevalence of 16%. Paray Mission hospital is situated in the central district Thaba Tseka with an estimated catchment population of 77’000 and an estimated HIV-prevalence of 20%. Routine ART and HTC services are offered at the hospitals and at the health centres belonging to the catchment areas (5 health centres in Seboche hospital and 7 in Paray hospital catchment area). Under the supervision of the professional and senior counselor, lay-counsellors perform HTC at hospital as well as health center level. The catchment populations of health centers vary between 4’000 and 10’000 in 20 to 60 main-villages that are sometimes again divided into up to 5 sub-villages.

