### Procedures

The procedures are defined in the Standard of Procedures (SOP) manual (see annex 1). Study-team-members have been instructed on the SOPs and conducted 4 pre-test campaigns under supervision. The pre-test villages belong to catchment areas that are not part of the study.

In case the team encounters severely ill clients with danger signs, the patients will be transported in the study-car to the hospital (Seboche or Paray hospital), see annex 1.

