### Collection and processing of data

During the testing campaign, data will be collected by the nurse, using a paper-based collection form (see annex 2). After the campaign a list of all clients tested HIV-positive and/or with a positive TB-screening will be created. Based on this list, data managers will visit the health centers 5 weeks after the campaigns and check in the registers, if these clients came to the facility to be enrolled into chronic HIV/AIDS care and/or to bring their sputum for smear-examination. (As mentioned in annex 1, patients who are expected to bring sputum to the facility and who do not appear at the facility within 5 days have to be traced immediately – bringing sputum after 5 days (through tracing or not) is considered as a negative outcome in the analysis).

Based on information of HTC- and pre-ART/ART-registers, data managers will collect data on absolute numbers newly tested HIV-positive and newly enrolled in chronic HIV/AIDS care during the 4 weeks after the campaigns from each cluster.

Data will subsequently be entered into an EpiData 3.1® database, using double-entry in order to ensure accuracy of data. On the paper records the patient-names appear (as they are needed to verify if the patient came for further care at the facility). However, the names are replaced by a code-identifier before being entered for analysis. The electronic database does not contain any patient-names. The paper-records are stored in locked cupboards at the two SolidarMed site-offices.

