| **TB-screening** | TB-screening has to be done to all clients (HIV-negative and HIV-positive).  **Do screening as follows:**  **HIV-negative adult/adolescent person:**   - Are you coughing since more than 2 weeks? - Have you lost weight? - Do you have drenching/soaking sweats at night? - Do you have fevers?   🡪 if the answer of any of these questions is yes 🡪 tick TB-screening positive, assess the patient and provide 3 sputum bottles.  **HIV-negative infant/child:**   - Is the child coughing since more than 2 weeks? - Has the child unexplained fever for more than 3 days? - Does the child have failure to thrive/faltering growth or signs of severe malnutrition? - Has the child been in contact with someone with smear + TB?   🡪 if the answer of any of these questions is yes, tick screening positive, assess child for any danger signs and refer for MD-assessment.  **HIV-positive adult:**  Are you coughing?   - Have you lost weight? - Do you have drenching/soaking sweats at night? - Do you have fevers?   🡪 if the answer of any of these questions is yes, tick TB-screening positive, assess the patient and provide 3 sputum bottles.  **HIV-positive infant/child:**   - Is the child coughing? - Has the child fever? - Does the child have failure to thrive/faltering growth or signs of severe malnutrition? - Has the child been in contact with someone with smear + TB?   🡪 if the answer of any of these questions is yes, tick screening positive, assess child for any danger signs and refer for assessment by medical doctor at the hospital.  **Sputum-collection:**   1. Instruct TB-suspect on sputum collection 2. Fill out sputum request form 3. TB-suspect shall provide one on-the-spot sputum outside the house 4. TB-suspect shall bring the 3 bottles to the HC the following day 5. Note the clients in the TB-suspect register at the health center 6. Instruct health center to trace the TB-suspect, if he/she does not bring the sputum bottles within 5 days (the health centers can use the SolidarMed tracing fund) |
| --- | --- |
| **Sputum bottles given** | Provide 3 sputum bottles to each adult patient with positive TB-screening. If sputum-bottles provided 🡪 tick Yes. |

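### Enrolment into HIV care, the third primary outcome, has no facility restriction but is looked up only in health-center registers, so enrolment at the two hospitals (or possibly at another study health center) is recorded as not enrolled.

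*Protocol*

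**What the plan says.** In Table 2 of the Protocol (Outcomes measured), the third primary outcome is the proportion and number "newly enrolled on chronic HIV/AIDS care within one month after the campaign of those newly tested during campaign". No facility is named. The aim and the main objective are worded just as broadly. The outcome is coded yes or no.

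The text above that table gives the sources as the study questionnaire and "the following official registers at the health centers: HTC-register, pre-ART register, ART-register, tuberculosis-suspect register". The section on collection and processing of data describes the look-up: "data managers will visit the health centers 5 weeks after the campaigns and check in the registers, if these clients came to the facility". Hospital registers are not mentioned there or anywhere else. Nor does the text say whether a client missing from the registers of one health center is looked for at the other eleven.

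The Study setting section says: "Routine ART and HTC services are offered at the hospitals and at the health centres belonging to the catchment areas".

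Annex 1 has a referral form completed for each positive client and a list of new positives given to the health center. That center traces clients who have not appeared within one month.

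**The concern.** The outcome as defined is wider than the outcome as measured. ART is available at 14 facilities (12 health centers and two hospitals), and registers are read at the health centers only. A client who takes up care at a hospital has met the definition but will not be found.

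The effect is one-sided misclassification: true enrolments are turned into failures and never the reverse. This is a primary outcome, and its denominator is only the clients who newly test positive, so a handful of missed enrolments is visible in the result. A later analysis plan cannot repair it, because the information sits in registers that nobody was asked to open.

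**Working it through.** **1. Does any other source close the gap?**

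- *Questionnaire.* It is named as a source, but Annex 2 leaves its outcome fields empty at the campaign, except for clients already registered in care. The fields are filled in later, so they are not independent of the register look-up. They have no entry for place of enrolment and no category for enrolled elsewhere.
- *Tracing.* It is done by the health center for clients who have not appeared there after one month, so it begins as the outcome window closes. No text feeds its findings into the outcome.
- *Table 2 cell.* It says only pre-ART and ART registers, but the sentence above the table places these at the health centers, and the data-collection section repeats that location.
- *Cluster-level counts.* These come from the registers of each cluster, and a cluster is a health center with its catchment area.

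None of these captures hospital enrolment. With a yes/no variable and no other source, a client not found is a no. The Protocol does not state this scoring; it follows from the coding and the sources.

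**2. Is there a planning figure to reproduce?**

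Not for this outcome. The sample size section concerns HTC uptake only (80% versus 65%, k = 0.1, 200 clients per cluster). The unmatched Hayes and Bennett formula with a two-sided 5% level and 80% power gives 5.38, which rounds up to the stated 6 clusters per arm. That agrees, but it has no bearing on enrolment.

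**3. Size if the loss is equal in both arms**

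Let h be the share of truly enrolled clients who register only at a facility whose registers are not searched. Then

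observed enrolment = true enrolment × (1 − h), and observed difference = true difference × (1 − h).

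The Protocol gives neither h nor an expected enrolment rate. For illustration, assume true enrolment of 50% (door-to-door) and 35% (pitso):

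| h (assumed) | Door-to-door | Pitso | Difference | Odds ratio |
| --- | --- | --- | --- | --- |
| 0% | 50.0% | 35.0% | 15.0 points | 1.86 |
| 10% | 45.0% | 31.5% | 13.5 points | 1.78 |
| 20% | 40.0% | 28.0% | 12.0 points | 1.71 |
| 30% | 35.0% | 24.5% | 10.5 points | 1.66 |

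An example of the last column, at h = 10%: (0.45/0.55) ÷ (0.315/0.685) = 1.78. The ratio of proportions stays at 50/35 = 1.43 throughout. The absolute difference shrinks in proportion to h. The odds ratio, which the planned logistic regression estimates, moves towards 1 more slowly.

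**4. How much does one missed enrolment weigh?**

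A generous upper figure for positives per arm takes 6 × 200 = 1,200 clients, 65% to 80% tested, and the full catchment prevalence of 16% to 20%:

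- low end: 1,200 × 0.65 × 0.16 = 124.8
- high end: 1,200 × 0.80 × 0.20 = 192

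The real number should be lower, because clients already known to be positive are excluded from the primary outcomes. Even so, one missed enrolment moves an arm by 1/192 = 0.5 to 1/124.8 = 0.8 percentage points, and five move it by 2.6 to 4.0 points.

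**The case against.** The strongest reply is that the Protocol's own HIV pathway leads to the health center. Positive clients are referred there, it holds the list and does the tracing, all facilities involved are certified ART centers, and study villages lie clearly inside one catchment area. Looking for enrolment where clients are sent is a coherent choice. This stands as a reason to expect a small loss. It does not remove the mismatch, because the outcome is not defined as enrolment at that health center.

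Two stronger readings are tempting, and the documents support neither.

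*That the plan itself sends clients to enrol at a hospital.* For severely ill clients with danger signs, "the patients will be transported in the study-car to the hospital". Clients with very high glucose are also taken to hospital, and the instruction for HIV-positive children with a positive TB screen is to "refer for assessment by medical doctor at the hospital". These are acute-care or assessment routes, and the glucose rule applies whatever the HIV status. None says that the client is registered for pre-ART or ART at the hospital. To be lost this way, a client must be newly positive, meet a narrow trigger, enrol at the hospital within one month and not appear in the registers of the own health center.

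*That the loss works against door-to-door.* A reader might infer that home visits find sicker people, who then go to hospital. The section on individual-level selection says only that door-to-door will probably reach different people, and Table 2 gives no directional hypothesis for WHO stage or CD4 count. The arithmetic is symmetric. With true enrolment of 50% in both arms, assumed shares of 15% (door-to-door) and 5% (pitso) give 0.50 × 0.85 = 42.5% versus 0.50 × 0.95 = 47.5%, a false deficit of 5 points. Swapping the shares gives a false gain of 5 points. By the labels in Table 1, each arm has three Seboche and three Paray health centers, so hospital area looks balanced. (The Study setting section counts five and seven, so the labels need checking.) Distance to hospital is not addressed.

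**Conclusion.** The point holds as a mismatch between a primary outcome and its data source. As written, a newly positive client who enrols at Seboche or Paray hospital is recorded as not enrolled. The same applies to a client who enrols at another study health center, if only the own center's registers are checked; the text leaves that open.

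The size is unknown. The Protocol gives no rate of enrolment elsewhere, and the default referral to the health center suggests that it may be low. If the loss is equal in both arms, enrolment is understated and the absolute difference shrinks by the same fraction: 10% for an assumed share of 10%, which takes 15 points to 13.5. A difference between arms in either direction is possible, but nothing in the documents shows one. The change is worth making because the outcome is primary, its denominator is small and the remedy is cheap. It is not evidence that the comparison is already biased.

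**What to change.** In the sections on sources of outcomes and on collection and processing of data:

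- add the pre-ART and ART registers of both hospitals and of the other study health centers as outcome sources;
- at the 5-week check, search them for every listed newly positive client not found at the own health center;
- count enrolment within one month at any of these facilities as enrolled;
- record the place of enrolment and report it by arm, so that any imbalance can be seen.

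The cost is a change of wording and some extra register time for the existing data managers. No patient contact and no change to care are involved.

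If the wider search is not feasible, restate the third primary outcome, and the matching objective, as enrolment at the cluster's own health center. Definition and measurement then agree, but the result no longer speaks to enrolment in care at large.

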## STUDY DESIGN

Prospective cluster-randomized study. Each health center within the SMART project area (n=12) with its catchment area represents a cluster. One study arm provides integrated HTC using the door-to-door approach (6 HCs) as compared to the other arm using the pitso-approach (6 HCs)

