### Randomization

The 12 health centers were openly randomized into two equal groups. Before randomization, clusters were stratified and paired according to their average-numbers of monthly new HIV-positive tested clients at routine clinic-based HTC (routine data from October to December 2010).

During an official meeting held on October the 3rd, a person not involved in the study threw a coin for one health center in each pair to allocate it either to the door-to-door or the pitso-arm. The other health center in the pair then automatically fell into the other arm. Table 1 shows the cluster-pairs and their allocation:

| **Pitso-arm** | **Door-to-Door arm** | **Time-frame of campaign** |
| --- | --- | --- |
| St Theresa HC (Paray) | St Peters HC (Seboche) | 17.-21. October 2011 |
| Ngoajane HC (Seboche) | Sehong Hong HC (Paray) | 24.-28. October 2011 |
| Linakeng HC (Paray) | Mokoto HC (Paray) | 31.10.-4.11. 2011 |
| Muela HC (Seboche) | Mohlanapeng HC (Paray) | 7.-12. November 2011 |
| Katse HC (Paray) | Boiketsiso HC (Seboche) | 14.-18. November 2011 |
| Khohlonso HC (Seboche) | Makhunoane HC (Seboche) | 21.-25. November 2011 |

Table 1 Matched pairs of clusters (health centers), their allocation to the study-arms and period where campaigns are held.

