## Sample size

Expected difference in HTC-uptake between study-arms (1^st^ primary outcome): 80% (door-to-door) versus 65% (pitso)

k= 0.1

Power: 80%; Significance level: 5%

clients per cluster: 200 (persons attending the services per cluster)

According to formula of Hayes & Benett^[[2]](#footnote-2)^: 6 clusters per arm

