## Statistical Analysis

All primary outcomes are binary variables. Absolute counts and proportions will be reported. To assess differences in primary outcomes, adjusted logistic regression will be used. All logistic regression models will be adjusted for clustering using the cl-command in STATA.

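### Age and CD4 count are assigned client-level t-tests or rank-sum tests that ignore the randomisation of 12 health centres, so their p-values will be too small

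*Protocol*

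**What the plan says.** The Protocol describes the trial as a "Prospective cluster-randomized study" and defines the unit under Study design: "Each health center within the SMART project area (n=12) with its catchment area represents a cluster". Under Randomization it adds: "Before randomization, clusters were stratified and paired according to their average-numbers of monthly new HIV-positive tested clients". The Sample size section arrives at "6 clusters per arm", using a between-cluster coefficient of variation k of 0.1 and 200 attenders per cluster.

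Table 2 lists two continuous secondary outcomes: age of clients attending HTC, and average CD4 count of clients newly tested HIV-positive. For age the method is "t-test/ranksum test", and the CD4 row names the same two tests. Every other row is assigned logistic regression. The age row carries a directional hypothesis (younger clients under door-to-door); the CD4 row carries none.

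The Statistical Analysis section contains the only statement on clustering: "All logistic regression models will be adjusted for clustering using the cl-command in STATA". Nothing in the Protocol mentions cluster means, a paired test or any adjustment for the two continuous outcomes.

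**The concern.** A two-sample t-test or rank-sum test takes each observation as independent. Here clients come from the same health-centre catchment, the same five villages and, in the door-to-door arm, the same households. The treatment was assigned to 12 units, so chance differences between catchments are part of the error against which the arms must be compared. A client-level test leaves that error out.

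The Protocol is also inconsistent with itself. It allows for between-cluster variation in the sample size and adjusts every logistic model. Sex of testers is therefore adjusted while age is not, and WHO stage is adjusted while CD4 is not, although each pair answers the same kind of question.

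Age matters more than its place in the table suggests. The section on individual-level selection bias makes reaching a different population part of the study hypothesis and names age and gender as the differences to be assessed. An unadjusted test may present ordinary differences between catchments as evidence for that hypothesis.

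**Working it through.** **Inputs from the Protocol (Sample size; Study design).** Six clusters per arm; 200 attenders per cluster; expected HTC uptake 65% (pitso) and 80% (door-to-door); k = 0.1; power 80%; significance level 5%, taken as two-sided.

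**The plan's own figure.** The standard unmatched formula for two proportions in a cluster-randomised trial is

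c = 1 + (z₁₋α/₂ + z₁₋β)² × [p₀(1−p₀)/m + p₁(1−p₁)/m + k²(p₀² + p₁²)] / (p₀ − p₁)².

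With p₀ = 0.65, p₁ = 0.80, m = 200 and k = 0.1, the second term is 4.38, so c = 5.38, rounded up to 6. The stated figure reproduces, which confirms that the plan treats the health centre as the unit carrying between-cluster error.

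**Clients per centre for age.** 200 × 0.65 = 130 and 200 × 0.80 = 160, if all attenders are eligible for testing. At the planned rates the total is 6 × 130 + 6 × 160 = 1,740. A middle value of m = 150 is used for the formula.

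**Assumptions.** The Protocol gives no ICC for age or CD4 and no number of positives per centre. ICCs of 0.005 to 0.10 and 5 to 30 positives per centre are assumed. For orientation only, k = 0.1 implies an ICC for *uptake* of k²p/(1−p): 0.01 × 0.65/0.35 = 0.019 and 0.01 × 0.80/0.20 = 0.040. This does not measure clustering of age or CD4.

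**Formula.** Design effect DE = 1 + (m − 1) × ICC. True type I error of a nominal two-sided 5% test that ignores clustering = 2 × [1 − Φ(1.96/√DE)].

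**Age, m = 150:**

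| ICC | DE | True type I error |
|---|---|---|
| 0.005 | 1.745 | 13.8% |
| 0.01 | 2.49 | 21.4% |
| 0.02 | 3.98 | 32.6% |
| 0.05 | 8.45 | 50.0% |

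**Simulation check.** Six clusters per arm, normal data and no true difference; 8,000 runs for the t-tests and 2,000 for the rank-sum test. Entries are rejection rates at nominal 5%.

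| Outcome, m | ICC | Client t-test | Client rank-sum | t-test on 12 centre means |
|---|---|---|---|---|
| Age, 130 | 0.01 | 18.9% | 17.8% | 5.2% |
| Age, 130 | 0.02 | 30.1% | 29.4% | 5.0% |
| Age, 130 | 0.05 | 47.6% | 45.5% | 5.1% |
| Age, 160 | 0.01 | 22.2% | 21.1% | 5.0% |
| Age, 160 | 0.02 | 34.0% | 33.5% | 5.3% |
| Age, 160 | 0.05 | 51.4% | 50.5% | 5.0% |
| CD4, 7 | 0.02 | 6.5% | 6.1% | 5.3% |
| CD4, 7 | 0.10 | 12.5% | 12.6% | 4.9% |
| CD4, 15 | 0.05 | 13.5% | 11.5% | 4.9% |
| CD4, 30 | 0.10 | 32.0% | 33.5% | 5.5% |

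At ICC 0 both client-level tests hold about 5%, so the inflation comes from clustering alone. Choosing the rank-sum test does not help. Across all scenarios the unpaired t-test on centre means stayed between 4.7% and 5.5%.

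**CD4 by formula, 5 to 10 positives per centre.** At m = 5 and ICC 0.02, DE = 1 + 4 × 0.02 = 1.08 and the error is 5.9%. At m = 10 and ICC 0.10, DE = 1 + 9 × 0.10 = 1.90 and the error is 15.5%.

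**The case against.** The strongest reply has four parts.

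- **Secondary outcomes only.** The three primary outcomes use cluster-adjusted logistic regression, and the sample size rests on uptake. This is true, and it limits the consequence. It does not make the named test valid.
- **The unit of the t-test is not stated.** A t-test on centre means would be sound, and a statistical analysis plan that is not shown might say so. But the list of collected variables has age and CD4 as continuous measurements on each client, Table 2 marks them as continuous, and the clustering sentence is confined to logistic models. The client-level reading is the natural one. The Protocol names a specific test, so this is more than detail left for later, and an analysis plan that followed it would carry the error forward.
- **The size depends on ICCs that the Protocol does not give.** This stands. The percentages are conditional on the assumed range, and the ICC implied by k concerns uptake only. Even at the lowest age ICC considered, 0.005, the error is nearly three times nominal.
- **CD4 is little affected.** With few positives per centre and a small ICC this is right: about 6% is close to nominal. With 30 positives and an ICC of 0.10 it reaches 32%, so CD4 cannot be called safe in advance.

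Two smaller points also stand. Known positives and clients in the window period are not eligible for testing, so the counts per centre for age are upper figures at the planned attendance. Household dependence is real in the door-to-door arm but is not in the calculation.

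**Conclusion.** The concern holds. The Protocol assigns two client-level outcomes tests that ignore its own unit of randomisation, and its only clustering provision does not reach them. For age, the true type I error of the nominal 5% test is about 14% to 50% over ICCs of 0.005 to 0.05 with about 150 testers per centre. For CD4 it is about 6% to 16% with 5 to 10 positives per centre and ICCs of 0.02 to 0.10, and higher if positives are more numerous. Confidence intervals built on the same standard errors would be too narrow by a factor of √DE, for age √1.745 = 1.3 to √8.45 = 2.9. All ICCs, and the number of positives per centre, are assumptions. The main harm is to age, because it carries a directional hypothesis. The primary analyses are untouched by this point.

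**What to change.** In Table 2, replace the method in the age and CD4 rows with a comparison of health-centre summaries: mean age per centre, and median or mean log CD4 per centre, by a paired t-test over the six randomised pairs (5 degrees of freedom). This follows the paired allocation. The simulation above covers only the unpaired version on 12 means (10 degrees of freedom), which held its size; if pairing is thought to cost too much for these outcomes, that version should be named in advance.

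Alternatively, specify a linear mixed model with a health-centre random effect and small-sample degrees of freedom. This may suit CD4 better if some centres have very few or no new positives, since a centre without a summary removes its pair from the paired test. A linear regression with cluster-robust standard errors would sit closest to the existing text, but needs a small-sample correction for 12 clusters.

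In Statistical Analysis, add one sentence stating that the continuous outcomes are also analysed with the health centre as the unit of clustering, and by which of these methods.

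The cost is two table cells and one sentence. No new data are needed, because each client's health centre is already known. The intervals for age and CD4 will be wider, which reflects the information that 12 clusters provide.

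### The sputum-return proportion counts screen-positive children in its denominator, although the procedures give them no sputum bottles to return

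*Protocol*

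**What the plan says.** Protocol, Outcomes measured, Table 2, lists as a secondary outcome "Absolute number and proportion of clients positively screened for tuberculosis who bring their sputum to the facility within ≤ 5 days", to be analysed by logistic regression. The row sets no restriction by age or by whether bottles were handed out.

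Annex 1 (TB-screening row) sets out who is screened and what follows:

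- Everyone is screened: "TB-screening has to be done to all clients (HIV-negative and HIV-positive".
- For adults (and adolescents, in the HIV-negative pathway), any positive answer leads to "tick TB-screening positive, assess the patient and provide 3 sputum bottles".
- For an HIV-negative child the instruction is "tick screening positive, assess child for any danger signs and refer for MD-assessment".
- For an HIV-positive child it is "tick screening positive, assess child for any danger signs and refer for assessment by medical doctor at the hospital".
- The separate row on bottles reads "Provide 3 sputum bottles to each adult patient with positive TB-screening".

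Collection and processing of data says how follow-up is organised: "After the campaign a list of all clients tested HIV-positive and/or with a positive TB-screening will be created". Data managers take that list to the health centres five weeks later. The same section counts sputum brought after five days as a negative outcome.

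**The concern.** A return rate should be measured among people who were asked to return something. Here the denominator is set by the screening tick and the numerator by the bottles, and for children the two do not go together. A screen-positive child handled exactly as Annex 1 requires looks the same in the analysis as an adult who took bottles home and never came back.

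Two things are at stake. The proportion in each arm no longer describes how well sputum return works. The comparison between arms also picks up the age mix of screen-positive clients. The Protocol gives reason to think that mix may differ. Door-to-door offers the package to household members of every age (Selection of individuals), and the section on individual-level bias makes reaching a different population part of the hypothesis. A difference in who was screened could then be reported as a difference in who returned sputum.

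**Working it through.** **Does anything else in the Protocol repair the denominator?**

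- The follow-up list covers all screen-positives, children included.
- The remark in the same section about patients expected to bring sputum concerns tracing and late returns. It does not redefine the denominator.
- The form (Annex 2) records sputum brought as yes or no, with no not-applicable box, although deworming, immunization, vitamin A and family planning each have one.
- The form has a yes/no field for sputum bottles given. That field is missing from the list of variables collected during campaigns, and no section uses it to restrict this outcome.
- Elsewhere the Protocol narrows a denominator when it means to. Known HIV-positive and recently tested clients are excluded from the primary outcomes, and the smear-result row of Table 2 is limited to clients who brought bottles.

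**Size.** The Protocol states no expected figure for this outcome. Its sample size rests on HTC uptake only, so there is no planned value to reproduce. Let r be the return rate among clients asked for sputum, and c the share of children among screen-positive clients. Children contribute nothing to the numerator, so

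proportion under Table 2 = r × (1 − c).

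Both r and c are assumptions. Take r = 0.60 in both arms, so that the true difference is zero:

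| c, one arm | c, other arm | Proportions | Difference | Odds ratio |
|---|---|---|---|---|
| 10% | 10% | 54% v 54% | 0 | 1.00 |
| 10% | 20% | 54% v 48% | −6 points | 0.79 |
| 10% | 30% | 54% v 42% | −12 points | 0.62 |
| 10% | 40% | 54% v 36% | −18 points | 0.48 |

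For the third row: 0.60 × 0.90 = 0.54 and 0.60 × 0.70 = 0.42. The odds ratio is (0.42/0.58)/(0.54/0.46) = 0.62.

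Keeping 10% v 30% and varying r:

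- r = 0.40 gives 36% v 28%, −8 points, odds ratio 0.69.
- r = 0.80 gives 72% v 56%, −16 points, odds ratio 0.50.

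The share matters, not the number of children. Compare 90 adults and 10 children in one arm with 180 adults and 20 children in the other. At r = 0.60 the results are 54/100 and 108/200, both 54%, although the second arm reached twice as many children.

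With the denominator limited to clients asked for sputum, the proportion equals r in each arm, and the odds ratio is 1.00 whatever the child shares.

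**The case against.** **The text does not say that children fail.** No sentence codes a client without bottles as a non-returner. Table 2 names the tuberculosis-suspect register as a source, and Annex 1 places entry in that register among the sputum-collection steps. A sympathetic reader could take the outcome to cover only clients asked for sputum. This stands in part: an explicit rule failing every child cannot be quoted. But Table 2 does state the denominator, and the follow-up list matches it, so following the text as written has that effect. This is a stated definition that conflicts with the procedures, not a detail left open for a later analysis plan.

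**The sputum-collection steps carry no age limit.** They speak of TB suspects in general. However, neither child pathway mentions bottles, and the bottle row names adults.

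**A reader might infer that door-to-door is penalised because it reaches more children.** The documents do not support that. The age hypothesis ("Lower in door-to-door") is stated for clients attending HTC, not for screen-positive clients. A lower age there could reflect adolescents or young adults, and the HIV-negative pathway gives adolescents bottles. Pitso also serves everyone who attends. Children and adults are screened with different questions, so the child share among screen-positives cannot be deduced from who is reached. This objection stands in full.

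**Dividing simply by clients given bottles is not neutral.** It would hide eligible clients whom a team failed to supply, and supply is part of campaign delivery that could differ by arm. This also stands, and it shapes the fix.

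**Conclusion.** The denominator in Table 2 does not fit the procedures in Annex 1. If followed, it understates sputum return in any arm where children screen positive. It also biases the comparison between arms whenever the child share of screen-positives differs. On assumed values (60% return, child shares of 10% v 30%) the spurious gap is 12 points, odds ratio 0.62. Over return rates of 40% to 80% with the same shares it is 8 to 16 points. With equal shares and equal return there is no spurious difference.

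The Protocol supplies none of these rates and does not indicate which arm would have the larger child share, so no arm-specific penalty can be claimed. The absolute number bringing sputum is unaffected. The outcome is secondary, has no stated directional hypothesis and plays no part in the sample size. It is worth correcting, at modest priority.

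**What to change.** - In Table 2, define the denominator as screen-positive clients from whom the procedures request sputum, that is, those in the adult/adolescent pathway. Identify them from the age and bottles-given fields already on the form.
- Report by arm the proportion of these clients who were actually given bottles, so that a failure of supply stays visible.
- Give return among clients with bottles recorded as given as a supporting analysis.
- Report screen-positive children referred for assessment as a separate count by arm.
- Add the bottles-given field to the list of collected variables.

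The Annex 1 wording has to be reconciled first. The HIV-negative pathway groups adolescents with adults, while the HIV-positive pathway and the bottle row name adults only, and HIV-positive adolescents are not mentioned. Those responsible for the procedures must settle that; the analysis needs only a stated boundary.

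The cost is a revised Table 2 entry, a few reporting lines and a somewhat smaller denominator. No new data are needed.
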